### Study groups

#### In-hospital P.A.R.T.Y.

The In-Hospital P.A.R.T.Y. is a full day (6 h) harm minimisation and prevention program. Additional file 1: Appendix 2 describes the schedule of the in-hospital program. At the commencement of the program participants are provided with context talks from various health professionals, followed by interactive tours of the trauma centre, Intensive Care Unit and a ward area. These tours are facilitated by clinical staff in the areas and, in the case of the ICU and ward area, the participants also spend time with a family or patient. The afternoon is spent with Allied Health professionals who describe/show the effects of trauma to help participants better understand the consequences of disability following trauma. Overall, the program is designed to provide pertinent information to participants in order for them to be more aware of injury-producing situations, make informed prevention-orientated choices, and adopt behaviours and actions to minimise risk of injuries [7].

#### On-base P.A.R.T.Y.

The on-base P.A.R.T.Y. program is a four-hour adaptation of the in-hospital program. The content is consistent with the in-hospital program but the program is delivered by health professionals and trauma survivors, with the aid of simulation, in the health centre at the participating naval base. Additional file 1: Appendix 3 describes the schedule of the on-base program.

#### Annual awareness training

The ADF delivers a number of mandatory training modules to all personnel annually. One of these is an annual alcohol and other drug awareness program. The alcohol and other drug annual awareness training module is delivered by a designated and trained Alcohol and Other Drugs Program counsellor. This training typically consists of a PowerPoint presentation outlining the ADF/RAN responsibilities for all members and the organisation in relation to the sales and consumption of alcohol. The presentation takes approximately 1 h and is currently delivered as a face-to-face presentation.

### Measures

#### Primary outcome

The primary outcome measure will be the proportion of participants reporting an AUDIT score of 8 or above at 12 months’ post-intervention.

#### Secondary outcomes

The secondary outcome measure will be the number and time to alcohol related incidents in the 12 months’ post-intervention. All participants will be able to be followed up as a result of the ADF’s requirement of all members to report all civilian legal actions against them. This includes alcohol related offences.

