**Methods/design:**

The study is a 3-arm randomized controlled trial, involving 953 Royal Australian Navy trainees from a single base. Trainees, aged 18 to 30 years, will be randomly assigned to the study arms: i. in-hospital P.A.R.T.Y.; ii. On-base P.A.R.T.Y.; and iii. Control group. All groups will receive the routine ADF annual alcohol awareness training. The primary outcome is the proportion of participants reporting an Alcohol Use Disorders Identification Test (AUDIT) score of 8 or above at 12 months’ post-intervention. The secondary outcome is the number of alcohol related incidents reported to the Royal Australian Navy (RAN) in the 12 months’ post-intervention.

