#### Data analysis

Data will be analysed on a per-protocol and intention to treat basis. Summary statistics will be used to describe the difference between groups and ascertain if balance of groups has been achieved through the randomisation process. Frequencies and percentages will be used for categorical variables and mean and standard deviations, or median and inter-quartile range for continuous variables.

The primary outcome will be analysed using a modified Poisson regression model with a robust variable estimator [16]. The relative risk, and 95% confidence intervals (CI) of reporting an AUDIT score of 8 or above in the intervention groups will be calculated relative to the control group. Where necessary, the model will be adjusted for factors not balanced between the groups through the randomisation process.

The secondary outcome will be analysed using a Cox Proportional Hazards regression model assessing time to an alcohol related incident reported to the RAN, with participants not reported for an alcohol related incident censored at 12 months’ post-intervention. Where a participant leaves the RAN, these participants will be censored at the date of discharge from the RAN [16–18]. Hazard ratios, and 95% CI will be reported. For both analyses, multivariate models will be used if there is baseline imbalance between the groups.

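### The secondary outcome is defined three ways, and the one planned analysis, a Cox model, gives no between-arm estimate of the number of incidents

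*Protocol article*

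**What the plan says.** Three places in the protocol article describe the single secondary outcome.

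- Abstract, Methods/design: "The secondary outcome is the number of alcohol related incidents reported to the Royal Australian Navy (RAN) in the 12 months’ post-intervention". This is a count.
- Measures, Secondary outcomes: "The secondary outcome measure will be the number and time to alcohol related incidents in the 12 months’ post-intervention". This is a count and a time.
- Measures, Data analysis: "The secondary outcome will be analysed using a Cox Proportional Hazards regression model assessing time to an alcohol related incident reported to the RAN". This is a time only, with hazard ratios and 95% confidence intervals as the reported effect.

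Two censoring rules go with the Cox model. The first has "participants not reported for an alcohol related incident censored at 12 months’ post-intervention". The second is for people who leave the service: "these participants will be censored at the date of discharge from the RAN". The Secondary outcomes section nevertheless says "All participants will be able to be followed up", on the ground that ADF members must report civilian legal actions against them.

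**The concern.** A count and a time to event are different estimands. A Cox model that takes one event per person uses when that event happened and ignores any later ones. Two arms could have the same pattern of first incidents and different totals. The hazard ratio would then show no difference although the numbers differ.

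A reader of the abstract would expect the trial to say whether the program changes the number of incidents, and the Conclusion speaks of reducing alcohol related incidents in general terms. The stated analysis does not answer that question. With three wordings in print, it is also unclear which of them a later report should be held to.

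**Working it through.** **Step 1. Match each declared component to an analysis.**

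| Component | Declared in | Analysis in Data analysis | Effect measure |
|---|---|---|---|
| Number of incidents | Abstract; Secondary outcomes | None named | None |
| Time to an incident | Secondary outcomes | Cox proportional hazards | Hazard ratio, 95% CI |

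The modified Poisson model in Data analysis belongs to the binary AUDIT outcome and yields a relative risk, so it does not fill the empty row. The summary statistics promised there are general and linked to checking balance. They do not name incident counts and carry no effect estimate.

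**Step 2. Does the Cox model use repeat incidents?** The article does not say *first* incident. But it censors at 12 months those with no reported incident and says nothing of further time at risk after one. The natural reading is one event per person, so later incidents contribute nothing.

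**Step 3. How much might that leave out?** The plan gives no figure for this outcome, so there is none to reproduce. What follows is illustration only.

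Inputs: p, the proportion with at least one incident in 12 months, set at 0.14 (the pilot result in Background); 953/3, about 318 per arm (abstract); and a dispersion d, which the documents do not give and which is assumed.

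- Poisson counts: mean m = −ln(1 − p) = −ln(0.86) = 0.151.
- Negative binomial counts: m = [(1 − p)^(−d) − 1]/d.
- Share of incidents that are repeats = (m − p)/m.

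| Assumption | m at p = 0.14 | Repeat share at p = 0.14 | Repeat share at p = 0.05 (assumed) |
|---|---|---|---|
| Poisson | 0.151 | 7% | 2.5% |
| d = 1 | 0.163 | 14% | 5% |
| d = 3 | 0.191 | 27% | 10% |
| d = 5 | 0.225 | 38% | 14% |

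At p = 0.14 there would be about 318 × 0.14 = 44 first incidents per arm. The total would be about 48 under Poisson counts and about 72 at d = 5.

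The 14% comes from 108 at-risk trainees, among whom those with an earlier incident had the higher rate. The inclusion criteria here require no incident on record since joining, which points to a lower p. The last column uses 5% purely to show the effect of that.

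**Step 4. Is exposure equal?** The discharge rule means some participants will be observed for less than 12 months. Any comparison of numbers therefore needs person-time in the denominator. The Cox model already allows for this, but a plain count does not.

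**The case against.** The strongest reply is that this is a narrow matter of wording. The Measures section declares time as well as number, and time has a fully named analysis with both censoring rules and an effect measure. Data analysis fixes one model for the secondary outcome, which limits the room for choosing an emphasis after the data are seen. Counts could be tabulated under the general summary statistics, and the handling of repeat incidents may be set out in a full protocol or analysis plan that is not shown.

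Much of this stands. A reader might infer that the declared secondary outcome is never estimated at all. The documents do not support that, because the time component is estimated. A reader might also see a flat contradiction between complete follow-up and censoring at discharge. That is too strong: the reporting duty falls on members, someone discharged may no longer be one, and the discharge rule largely settles the matter. The follow-up sentence is loose rather than in conflict with the analysis. Nor does the article propose an unadjusted comparison of raw counts, and nothing in it says that repeat incidents matter more to the RAN than first ones.

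What does not stand is the appeal to detail left for later. The article does not defer the method. It says how the secondary outcome will be analysed, and that method does not deliver the quantity named in the abstract or the first half of the one named under Measures. A descriptive table would not give a between-arm estimate with a confidence interval.

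**Conclusion.** The point holds in a limited form. The three descriptions of the secondary outcome disagree, and no planned analysis compares the number of incidents between arms. This rests on the stated text alone, together with the natural reading that the Cox model takes one event per person.

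Its size cannot be fixed from the documents. The repeat shares of 7% to 38% are correct arithmetic for 14% with an incident and the dispersions tried, but a reader should not take them as a forecast. Every dispersion value is assumed, and the pilot population differs from this one. The inconsistency is worth correcting because it is cheap to remove and leaves a declared question unanswered.

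**What to change.** 1. Use one definition of the secondary outcome in the abstract, in Secondary outcomes and in Data analysis.
2. If the number of incidents is wanted, add a rate analysis: for example negative binomial regression, or Poisson regression with robust standard errors, with the log of person-time to 12 months or discharge as offset. Report rate ratios with 95% confidence intervals beside the hazard ratios, and label the Cox model as time to first incident. The choice of covariates is the trial team's and is not part of this point.
3. If the number is not wanted, define the outcome as time to first incident in all three places. No new model is then needed.
4. Qualify the follow-up sentence so that it promises follow-up to 12 months or to discharge from the RAN, whichever comes first, and report the number discharged in each arm.

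The cost is a few sentences and, under option 2, one extra regression on data already held. No new data collection is needed.

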#### Data analysis

Data will be analysed on a per-protocol and intention to treat basis. Summary statistics will be used to describe the difference between groups and ascertain if balance of groups has been achieved through the randomisation process. Frequencies and percentages will be used for categorical variables and mean and standard deviations, or median and inter-quartile range for continuous variables.

The primary outcome will be analysed using a modified Poisson regression model with a robust variable estimator [16]. The relative risk, and 95% confidence intervals (CI) of reporting an AUDIT score of 8 or above in the intervention groups will be calculated relative to the control group. Where necessary, the model will be adjusted for factors not balanced between the groups through the randomisation process.

The secondary outcome will be analysed using a Cox Proportional Hazards regression model assessing time to an alcohol related incident reported to the RAN, with participants not reported for an alcohol related incident censored at 12 months’ post-intervention. Where a participant leaves the RAN, these participants will be censored at the date of discharge from the RAN [16–18]. Hazard ratios, and 95% CI will be reported. For both analyses, multivariate models will be used if there is baseline imbalance between the groups.

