## Background

Almost all societies that consume alcohol experience related health and social problems [1]. Excessive alcohol consumption, and associated harm, is a major contributor to morbidity and mortality in Australia and other developed countries [1–3]. Therefore, interventions to reduce excessive consumption and associated harm are needed.

To reduce the occurrence and cost of substance abuse problems, it is important to intervene early before harmful patterns of substance use are established [4, 5]. One intervention that is commonly used in an effort to reduce alcohol related harm in young people is the P.A.R.T.Y. program. P.A.R.T.Y. is an in-hospital, injury awareness and prevention program which originated in Canada in 1986, and now operates in over 100 sites around the world.

P.A.R.T.Y. is a full day program that involves interaction, generally of school groups, with emergency services personnel, health professionals, and patients who have experienced trauma and survived. Holding the program within a hospital environment is expected to leave a significant and lasting impression of the consequences of preventable trauma and risk taking behaviours [6, 7] (Additional file 1: Appendixes 1 and 2).

Case-control studies have shown that attendance at P.A.R.T.Y. reduced major trauma presentations in senior school students in Canada [6], and recidivism in juvenile justice young offenders [7]. Further, a pilot cohort study explored the feasibility of delivering the P.A.R.T.Y. program to 108 ‘at risk’ naval trainees, and found that 12 months after program participation, 14% of participants had been reported for an alcohol related incident, with the rate of reported alcohol related incidents following the program higher for participants who had a pre-program incident on record ([name], [name], [name], [name] and [name]: Piloting an injury awareness and education program for reducing alcohol related harm in Navy Trainees, Submitted).

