#### Randomisation

Following completion of consent forms and baseline screening measures, consented participants will be randomly allocated in a 1:1:1 ratio to one of the three trial arms. Randomisation will be stratified by gender in block sizes of 3, 6, 9, 12 or 15 patients. Randomisation will take place at an individual level. The allocation will be performed by a designated person not involved in the conduct of the programs, measurement of the outcomes, or analysis of the data. An opaque envelope containing computer-generated (RALLOC, Stata12) random intervention allocation will be provided for each participant.

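### If P.A.R.T.Y. sessions induce correlated outcomes, the stated Poisson and Cox models, which name no clustering on session, will give active-versus-control intervals that are too narrow

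*Protocol article*

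**What the plan says.** **Allocation.** Under Randomisation the Protocol article says "Randomisation will take place at an individual level", with trainees "randomly allocated in a 1:1:1 ratio to one of the three trial arms".

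**Delivery.** The Background describes the program generically: "P.A.R.T.Y. is a full day program that involves interaction, generally of school groups, with emergency services personnel". Under In-hospital P.A.R.T.Y., "participants are provided with context talks from various health professionals, followed by interactive tours of the trauma centre, Intensive Care Unit and a ward area"; the ICU and ward visits also include time with a patient or family. Under On-base P.A.R.T.Y., "The on-base P.A.R.T.Y. program is a four-hour adaptation of the in-hospital program", given by health professionals and trauma survivors with simulation. Session size and number of sessions are not stated. All three arms, control included, also receive the annual alcohol and drug training, a face-to-face presentation of about one hour.

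**Analysis.** Under Data analysis, "The primary outcome will be analysed using a modified Poisson regression model with a robust variable estimator" (evidently a robust variance estimator). Relative risks with 95% confidence intervals compare the intervention groups with control. The secondary outcome uses a Cox model. No session or cluster term is named for either.

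**Sample size.** The Sample-size calculation gives 284 per group for an 8-point reduction from 20% at 80% power, raised to 310 for loss to follow-up. It mentions no design effect.

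**The concern.** This looks like an individually randomised trial of a group-delivered treatment. Trainees at the same P.A.R.T.Y. session share speakers, the patient or survivor they meet, facilitators and peers, and these can differ from one session to the next. Controls attend no P.A.R.T.Y. session. The design is then partially nested: outcomes may be correlated within sessions in the two active arms, with no counterpart in the control arm.

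In modified Poisson regression, the usual robust variance repairs the mismatch between a Poisson variance and a binary outcome. It does not pick up correlation between participants unless it is clustered on the unit that creates the correlation. The same applies to the Cox model. Individual randomisation spreads pre-existing class and base effects across the arms, but it does not remove correlation created afterwards by a shared session.

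At stake is the coverage of the intervals against control, on which the article says decisions about wider adoption will draw.

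**Working it through.** **1. Reproduce the plan's own figure.** With p0 = 0.20, p1 = 0.12, mean 0.16 and one-sided 5%:

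n = [1.645·√(2·0.16·0.84) + 0.842·√(0.20·0.80 + 0.12·0.88)]² / 0.08² ≈ 259.

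The continuity correction (n/4)·[1 + √(1 + 4/(0.08n))]² gives **284**, an exact match. The formula treats every participant as independent, so the sample size contains no allowance for sessions.

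**2. Inputs for the check.**
- From the article: 20% v 12%; 953 trainees in three arms; 10% loss. Hence 953/3 × 0.9 ≈ 286 analysed per arm.
- Assumed, because the article does not give them: session size m and within-session ICC. Three pairs are used: (10, 0.01), (15, 0.02) and (25, 0.05).

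**3. Formulas.** The design effect DE = 1 + (m − 1)·ICC applies to active arms only.
- Actual two-sided error rate v control at equal prevalence: 2[1 − Φ(1.96·√(2/(1 + DE)))].
- The same between the two active arms: 2[1 − Φ(1.96/√DE)].
- Ratio of true to planned SE of log RR at 20% v 12%: √[(4 + 7.333·DE)/(4 + 7.333)], where 4 = 0.80/0.20 and 7.333 = 0.88/0.12.
- Coverage of the nominal 95% interval: 2Φ(1.96/ratio) − 1.
- Two-sided power at n = 286: Φ(0.08/√[(0.16 + 0.1056·DE)/286] − 1.96).

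**4. Results.**

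| m, ICC (assumed) | DE | Type I v control | SE ratio, log RR | Coverage | Power | Type I, active v active |
|---|---|---|---|---|---|---|
| any m, ICC 0 | 1.00 | 5.0% | 1.00 | 95% | 75% | 5.0% |
| 10, 0.01 | 1.09 | 5.5% | 1.03 | 94.3% | 73% | 6.0% |
| 15, 0.02 | 1.28 | 6.6% | 1.09 | 92.9% | 70% | 8.3% |
| 25, 0.05 | 2.20 | 12% | 1.33 | 85.9% | 58% | 19% |

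The 75% in the first row is not a clustering effect. It arises because 284 reproduces only with a one-sided test, while the table uses a two-sided one.

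**5. Simulation, correlation created by sessions.** Settings were equal 20% prevalence and about 286 per arm. In two sets of runs, the ordinary robust variance gave type I error v control of 5.4%, 6.2–6.5% and 11.6–12.0% for the three pairs. A session-clustered variance with singleton controls gave 5.0–5.5% in the first two and 6.2% in the third. The third has only about 12 sessions per arm (286/25 ≈ 11.4), which is why a small-cluster correction is needed.

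**6. Simulation, correlation from intakes shared by all arms, no program effect.** The ordinary robust variance gave 4.9%, 4.4–4.8% and 4.0–4.1%, so it is not anti-conservative here. Session clustering with singleton controls and no intake adjustment gave 4.5–4.6%, 3.5–3.9% and 1.6–1.7%, so it over-corrects. The combination of session clustering and intake adjustment was not simulated.

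**The case against.** **The article may simply be silent.** It never says that the variance is at individual level, and clustering is one option in a regression command, which a full protocol or SAP could specify. This stands in part: the point concerns the models as stated, and a session-clustered variance in an unseen plan would settle it. The article does, however, name the model and its variance type, and its sample size reproduces only with an independence formula.

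**A reader might infer that the false-positive rate does exceed 5%.** The documents do not support that. Inflation needs session-specific effects that average to zero. If the program changes nobody's drinking, sessions induce no correlation and the ordinary test keeps its level. After a single session of four to six hours, with AUDIT measured 12 months later, the ICC may be small.

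**Group delivery is inferred.** This is true. Talks, tours and a scheduled multi-speaker program for about 318 trainees per arm (953/3) make it a fair inference, but no session size is given.

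**A reader might treat controls as sharing no sessions at all.** That is too strong. They attend no P.A.R.T.Y. session, but all arms receive the annual face-to-face training.

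**A reader might take the between-program figures, up to 19%, as the main result.** Data analysis specifies comparisons with control only. The Conclusion mentions a direct in-hospital versus on-base comparison, but no test is laid down for it.

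**Clustering can over-correct.** This stands where correlation comes from intakes common to all arms (step 6 of the working), and it shapes the fix.

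**Conclusion.** The point holds conditionally. As written, neither model names clustering on session. If P.A.R.T.Y. sessions induce correlation in the active arms, the active-versus-control intervals are too narrow; if they do not, there is no error. Under the assumed 10 to 15 per session and ICC 0.01 to 0.02, the type I error against control is about 5.5% to 6.6%, a modest departure. The 12% figure needs 25 per session and ICC 0.05, which is extreme and has no support in the article. A comparison between the two programs would be affected more (6.0% to 8.3% on the same modest assumptions), if it is made. All these sizes rest on assumed session sizes and ICCs and on the inference of group delivery. The change is still worth making because it is cheap and protects the primary interval.

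**What to change.** - Record the P.A.R.T.Y. session attended or assigned for each active-arm participant, and the intake for every participant.
- In both the modified Poisson and the Cox model, use a robust variance clustered on session, with each control as a singleton cluster and a small-cluster correction.
- Adjust both models for intake or recruitment period, so that differences between intakes shared by all arms are not counted as session clustering.
- In the intention-to-treat analysis, place non-attenders in the session for which they were scheduled.
- If the in-hospital versus on-base comparison is to be reported, use the same variance for it.

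The cost is two identifiers, which attendance and recruitment records should supply, and a few lines of model specification. Intervals widen only as far as the data show session correlation: little if the ICC is near zero, and about 3% to 9% in the SE of the log relative risk against control under the modest assumptions above.

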## Methods

### Setting

Participants for this study will be recruited from Initial Entry Trainees who are completing their specialist training at the RAN’s key training establishment in Victoria. The intervention (P.A.R.T.Y.) will be delivered at two settings; at The Alfred (‘in-hospital’) and at the participating naval base (‘on-base’).

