### Study design

In this non-blinded RCT, participants will be randomised to one of three arms:i.In-hospital P.A.R.T.Y. program and annual alcohol and other drugs awareness training;ii.On-Base P.A.R.T.Y. program and annual alcohol and other drugs awareness training; andiii.Annual alcohol and other drugs awareness training only (Fig. 1).

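### The incident analysis is timed from the program day, which controls and active-arm non-attenders do not have and which falls after randomisation, so it states no common origin for an intention-to-treat Cox model

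*Protocol article*

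**What the plan says.** All references are to the protocol article.

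- **Secondary outcomes:** the measure is "the number and time to alcohol related incidents in the 12 months’ post-intervention".
- **Data analysis:** the Cox model is specified "with participants not reported for an alcohol related incident censored at 12 months’ post-intervention". For those who leave the RAN, "these participants will be censored at the date of discharge from the RAN". The same section commits to both intention-to-treat and per-protocol analyses.
- **Primary outcome:** "the proportion of participants reporting an AUDIT score of 8 or above at 12 months’ post-intervention".
- **Setting:** "The intervention (P.A.R.T.Y.) will be delivered at two settings", namely the hospital and the base.
- **Study design:** the third arm receives "Annual alcohol and other drugs awareness training only". Both active arms receive that training too.
- **Annual awareness training:** "The ADF delivers a number of mandatory training modules to all personnel annually".
- **Randomisation:** "Following completion of consent forms and baseline screening measures, consented participants will be randomly allocated in a 1:1:1 ratio".

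The text gives no index date for controls, no interval between randomisation and the program day, and no rule for incidents or discharges that fall between the two.

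**The concern.** A time-to-event comparison by intention to treat needs one origin that every randomised participant has and that does not depend on what happens after allocation. Randomisation is such a date. The program day is not, for three reasons.

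1. Controls have no program day. The annual module does not clearly stand in for it: all arms receive it, and its date relative to randomisation is not given.
2. A trainee allocated to P.A.R.T.Y. who never attends has no program day either, yet intention to treat must include that trainee.
3. The program day comes after randomisation. In the active arms, an incident in the gap lies before the window. A trainee discharged in the gap would be censored before time zero and contribute nothing.

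If controls are then given a different kind of start date, the arms are observed over different stretches of time since randomisation. Should incident risk change over the early months of training, part of any hazard ratio would reflect that difference and not the program.

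**Working it through.** **Plan's own figure.** There is none for this point. The sample size (284 per group) concerns the AUDIT proportion and does not depend on the time origin.

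**Applying the stated rule to each kind of participant**

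| Participant | Program day exists? | Start of 12 months under the stated rule |
|---|---|---|
| Active arm, attends | Yes, after randomisation | Program day |
| Active arm, never attends | No | Not defined |
| Active arm, discharged before the program | No | Not defined; the censoring date precedes any start |
| Control | No | Not defined |

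Only the first row can be analysed as written.

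**Illustration of size. Inputs**

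- 12-month risk of a first incident: 14%, from the pilot described in the Background. The pilot enrolled 108 at-risk trainees, whereas this trial excludes anyone with an incident on record, so 14% may be too high. I also show 5% and 20%.
- Gap g between randomisation and program: assumed 4, 8 or 12 weeks. The document gives no figure. The upper end borrows the minimum 12 weeks on base from the inclusion criteria.
- Arm size: 310, the recruitment target per group in the sample-size section.
- No program effect.

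**Step 1: incidents falling in the gap, constant hazard.**

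Weekly hazard λ = −ln(1 − 0.14)/52 = 0.0029. Expected number = 310 × (1 − exp(−λg)).

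| 12-month risk | g = 4 | g = 8 | g = 12 |
|---|---|---|---|
| 5% | 1.2 | 2.4 | 3.6 |
| 14% | 3.6 | 7.1 | 10.6 |
| 20% | 5.3 | 10.5 | 15.6 |

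**Step 2: ratio of cumulative hazards, active to control.**

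This step adds the assumption that controls are timed from randomisation (weeks 0 to 52) and active participants from the program day (weeks g to 52 + g). Let the hazard be mλ in weeks 0 to 12 and λ afterwards.

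- Control: λ(12m + 40).
- Active: λ(m(12 − g) + 40 + g).
- λ cancels, so the ratio does not depend on the 14%.

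| Early hazard | Ratio | g = 4 | g = 8 | g = 12 |
|---|---|---|---|---|
| Constant (m = 1) | 52/52 | 1.00 | 1.00 | 1.00 |
| Doubled (m = 2) | (64 − g)/64 | 0.94 | 0.88 | 0.81 |
| Halved (m = 0.5) | (46 + 0.5g)/46 | 1.04 | 1.09 | 1.13 |

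Hazards are not proportional in the last two rows, so these ratios are only a rough guide to what a Cox model would report.

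**The case against.** **The rule fixes an end, not a start.** The censoring sentence says when event-free follow-up stops and does not name Cox time zero. That is true of the sentence alone. The Secondary outcomes section, however, defines the window as the 12 months after the intervention, which fixes both ends, and the censoring rule matches it.

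**This is shorthand in a condensed article.** The full protocol or analysis plan may give controls a matched or scheduled session date, and the flow chart is not shown. This carries weight as to what will actually be done. But the article does not merely omit an origin. It states one repeatedly, and that origin cannot be applied to one arm and sits badly with intention to treat.

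**Everyone can be followed up.** The Secondary outcomes section says so, and nothing here disputes it. Follow-up being available does not settle when it begins.

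**A stronger reading is tempting.** A reader might infer that early incidents are dropped in the active arms only, and that the analysis is therefore biased towards the program. The document does not support this. It nowhere says that controls are timed from randomisation. With a matched index date for controls, early incidents would be left out of all arms alike. Even with different origins, a constant hazard gives a ratio of 1.00, and a lower early hazard moves the ratio against the program. The gap itself is unknown and could be short.

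**The primary outcome is hardly touched.** This stands. It is one AUDIT score at about 12 months, so no events are lost.

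**Conclusion.** The point holds for the secondary outcome. The stated origin does not exist for controls or for active-arm non-attenders. Where it does exist it falls after randomisation, leaving pre-program incidents and discharges outside an analysis described as intention to treat.

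Neither the size nor the direction of any bias follows from the document. The ratios of 0.81 to 1.13 rest on an assumed gap, an assumed hazard shape and an assumed control start date; they show only that the choice could matter in either direction. For the primary outcome the issue is at most an assessment date that differs between arms by an unknown amount. The flaw should be corrected before the incident data are analysed, but it does not undermine the main comparison and ranks below faults that do.

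**What to change.** **Incident analysis.** For the intention-to-treat Cox model, set time zero at the date of randomisation in all three arms. Count every incident from that date, and censor at 12 months after randomisation or at discharge from the RAN, whichever is earlier. Use the same window for the number of incidents. Keep an analysis from the program day as supportive only. Amend the wording in the Abstract, Secondary outcomes and Data analysis sections to match.

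One pre-specified index date that also applies to controls and non-attenders would give a common origin too. Unless it coincides with randomisation, it would still leave early incidents and discharges out of the intention-to-treat analysis.

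**Primary outcome.** State the 12-month AUDIT target from the same origin in all arms. Recruitment was scheduled to end in May 2016, so visits may already be fixed or done. In that case, report the time from randomisation to AUDIT by arm.

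**Cost.** For incidents, a change of wording and a re-cut of service records from a date that should be held for everyone. The downside is slight dilution of any program effect, because active-arm follow-up will include some pre-program time.
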